## Abstract

**Background:**

Protein-energy wasting (PEW) is common in hemodialysis patients and is a powerful predictor of morbidity and mortality. Although much progress has been made in recent years in identifying the causes and pathogenesis of PEW in hemodialysis patients, actual management by nutritional interventions is not always able to correct PEW*.* Some investigators suggest that physical exercise may increase the anabolic effects of nutritional interventions, and therefore may have a potential to reverse PEW. The aim of this study is to investigate the effect of intra-dialytic progressive exercise training and adequate nutritional supplementation on markers of PEW, functional capacities and quality of life of adult hemodialysis patients.

**Methods and design:**

Fifty end-stage renal disease patients undergoing hemodialysis, who meet the diagnostic criteria for PEW, will be randomly allocated into an *exercise* or *control* group for 6 months. The exercise consists of a progressive submaximal individualized cycling exertion using an adapted cycle ergometer, during the three weekly dialysis sessions. Biological markers of nutrition (albumin, prealbumin) will be followed monthly and all patients will be assessed for body composition, walk function, muscle strength, postural stability and quality of life at baseline and during the eighth week (t_+2_), the sixteenth week (t_+4_) and the twenty-fourth week (t_+6_) of the 6-month adapted rehabilitation program.

**Discussion:**

The successful completion of this current trial may give precious clues in understanding PEW and encourage nephrologists to extend prescription of exercise programs as well as therapeutic and as preventive interventions in this high-risk population.

**Trial registration:**

The protocol for this study was registered with the France Clinical Trials Registry NCT01813851.

## Background

Nowadays, more than two million people are treated worldwide by dialysis for end-stage renal failure [1]. Despite significant progress in dialysis techniques and in the treatment of associated comorbidities, hemodialysis (HD) patients experience an impairment of their quality of life and have a much higher risk of mortality compared to an age-matched population. A sedentary lifestyle and an altered nutritional status have been identified as major risk factors for adverse outcomes in dialysis patients [2,3].

Dialysis patients have decreased physical functioning (assessed by peak oxygen consumption ($\dot{V}O2\max$), physical performance tests, and self-reported functioning), diminished muscle mass and altered muscle quality, and all of these features are associated with an increased mortality risk [4-6]. These disturbances are directly related to renal failure and comorbidities, and also to adverse effects from medical treatments and from the dialysis itself. Dialysis induces notable metabolic changes: hypovolemia due to ultrafiltration, and rapid changes in electrolyte concentrations and systemic inflammation, which can all adversely affect physical function [7]. In addition, dialysis imposes immobilization over 12–18 hours a week, thereby directly contributing to sedentary behavior that can further worsen the medical condition of HD patients. This vicious circle can finally lead to the development of disability, loss of independence, and death [8]. For all these reasons dialysis patients have low levels of daily physical activity [9]. Therefore, it seems rational to promote programs for exercise training in this population.

In this vein, a large amount of literature published in the past 30 years has documented a myriad of potential benefits from exercise. Several include: increased maximal oxygen uptake capacity ($\dot{V}O2\max$), improved blood-pressure control [10], decreased arterial stiffness [11], decreased systemic inflammation [12], improved solute removal by dialysis [13,14], increased muscle mass, quality and force [15], and favorable psychological adaptations (e.g., higher perceived quality of life) [16]. Thus there is a large body of evidence that the impact of end-stage renal disease (ESRD) can be – for at least a significant part - counteracted by exercise training [7,17-20].

Along with this altered overall physical functioning, malnutrition is highly prevalent in the ESRD population, and is well-documented to be a strong predictor of mortality. Significant evidence comes from the data of large observational trials (USRDS, DOPPS [1-21]) showing that malnourished dialysis patients have an increased risk of mortality [22,23]. In this context, the International Society of Renal Nutrition and Metabolism (ISRNM) has recommended the term “protein–energy wasting” (PEW) to describe the loss of body protein mass and fuel reserves and have defined the diagnostic criteria for this state (see Table 1).

**Table 1 T1:** ISRNM criteria for the clinical diagnosis of PEW in maintenance dialysis patients

**Criteria***	
*Serum chemistry:*	
	Serum albumin < 3.8 g per 100 ml
	Serum prealbumin < 30 mg per 100 ml
	Serum cholesterol < 100 mg per 100 ml
*Body mass:*	
	BMI < 23
	Unintentional weight loss over time: 5% over 3 months or 10% over 6 months
	Total body fat percentage < 10%
*Muscle mass:*	
	Muscle wasting: reduced muscle mass 5% over 3 months or 10% over 6 months
	Reduced mid-arm muscle circumference area (reduction > 10% in relation to 50^th^ percentile of reference population)
	Creatinine appearance
*Dietary intake:*	
	Unintentional low dietary protein intake <0.80 g.kg^-1^.day-1 for at least 2 months
	Unintentional low dietary energy intake <25 kcal.kg^-1^.day-1 for at least 2 months

*At least three out of the four listed categories (and at least one test in each of the selected category) must be satisfied for the diagnosis of kidney disease related PEW. Optimally, each criterion should be documented on at least three occasions, preferably 2-4 weeks apart.

ISRNM, international society of renal nutrition and metabolism; PEW, protein-energy wasting; BMI, body mass index.

All these criteria are individually associated with an increased risk of adverse outcome so it can be assumed that the concomitant presence of at least three criteria is an even more powerful predictor of morbidity and mortality. However, to the best of our knowledge, until now no report exists about the prevalence and clinical outcomes of PEW (as defined by the ISRNM). It can be noted, however, that a large observational French study reported that 36% of HD patients had a prealbumine < 300 mg/dl, 20% had albumin < 35 g/l and 62% a diminished lean body mass (LBM) < 90% [24].

The mechanisms causing PEW are complex and multifactorial: low nutrient intake (sometimes due to dietary restriction), loss of nutrients into dialysate, abnormalities that stimulate protein degradation and/or decrease protein synthesis. On this last point, we can include the production of inflammatory cytokines, oxidative and carbonyl stress, endocrine disorders (hyperparathyroidism, hypogonadism, diabetes, decreased insuline/insuline like growth factor (IGF) signaling), acidosis, electrolyte imbalance, and anemia [25]. Further, low daily physical activity causes the loss of muscle mass and force and thereby directly contributes to worsen PEW. Traditional management of PEW according to international guidelines (coming from the EBPG working group on nutrition [26]) consists of dietary counseling, oral nutritional supplements, enteral feeding, and in severe cases, the use of intradialytic or total parenteral nutrition. Several studies, however, have shown that these interventions are not always able to correct PEW [27].

Simultaneously, considerable literature has pointed out the anabolic effects of physical activity. For example, both strength and endurance exercise induce transcriptional changes in genes (IGF, myostatin) favoring anabolic muscle [28]. Morevover, histologic and computed tomography studies have clearly demonstrated a decrease in muscle atrophy and an improvement of the overall muscular structure and quality (increased proportion of type II, oxydative fibers) [29]. There is also some evidence that intradialytic exercise, combined with oral or parenteral nutrition, enhances amino acid uptake and protein accretion in the muscles of HD patients [30,31]. Strong arguments exist for programming the adapted exercise training during the dialysis session rather than on non dialysis days, as there is better adherence by patients who feel safer doing exercise under medical monitoring, as a the counteraction to the inactivity due to the dialysis session, and due to a greater removal of uremic toxins (as shown for urea (KT/V) and phosphorous) by improved tissue mobilization. In addition, according to the large amount of published clinical trials, the risks of prescribing exercise even in this frail population are limited and the benefits largely prevail. Musculoskeletal injuries and cardio-vascular events are the most common risks of physical exercise. Both types of adverse events occur more frequently with high-intensity exercise than with submaximal exercise [32]. In this present trial, patients will be advised to exercise at a moderate level of perceived exertion and will be under continuous supervision by medical personnel. It should also be mentioned that European guidelines on nutrition in HD patients explicitly recommends regular physical exercise [26].

In sum, there are strong arguments in the literature to prescribe exercise in HD combined with nutritional interventions in patients suffering from PEW in an attempt to enhance the anabolic effects of nutrition and hereby reverse this high-risk state.

### Specific aims

The aim of this randomized controlled trial is to analyze the impact of a progressive intra-dialytic exercise program combined with nutritional support following current guidelines on nutritional parameters defined for PEW and its potential to reverse PEW. In addition, this trial will study the effect of intradialytic exercise on functional performance (walking, postural control, and muscular strength), body composition and health-related quality of life in HD patients.

## Methods and design

### Study design

This study is a multicenter, open-label randomized controlled trial. The study will be conducted at the outpatient HD Laennec Dialysis unit and Confluent Dialysis unit of the ECHO Dialysis Association. HD patients will be randomly distributed into a *control* or an *exercise* group. The randomization sequence of the participants will be generated by a computer program. A bio-statistician not involved in recruitment and assessment will perform the randomization.

The present study was approved by the Ethical Committee of Nantes Ouest IV (reference: ID RCB n°2012-A01662-41), and was conducted in accordance with the Declaration of Helsinki (last modified in 2004). All participants will receive written and verbal information about the aims and procedures of the study and will sign a consent form to participate in the study.

### Participants’ recruitment

All of the 210 patients treated by hemodialysis or online-hemodiafiltration in the participating centers will be screened for the presence of criteria for PEW. The principal investigators will review the existing patients’ database for serum albumin, serum prealbumin, C-reactive protein (CRP) levels*,* body mass index (BMI) and the presence of weight loss according to the PEW criteria. Potential subjects will have additional tests (measure of lean body mass index by bio-impedance and a 3-day dietary record by a qualified dietician in order to evaluate their protein and energy intake). Patients fulfilling inclusion/exclusion criteria and having signed an informed consent for the study participation will undergo randomization generated by a computer program. We expect to recruit approximately fifty HD patients for this study.

### Inclusion criteria

•Adult patients, male or female (Age > 18 years).

•Minimum hemodialysis vintage of 3 months.

•Stable on HD, in gender.

•No recent hospitalization.

•No acute or chronic medical conditions that would make exercise training potentially hazardous or primary outcomes impossible to assess.

•Patients who meet the following criteria for PEW (according to [25]), meeting at least three out of the four listed categories and at least one test in each of selected category:

–
*Serum chemistry criteria*: Serum albumin level < 38 g/L (Bromcresol Green), or serum prealbumin < 300 mg/L,

–
*Body mass criteria*: BMI < 23 kg/m^2^, or unintentional weigh loss > 5% over 3 months or > 10% over 6 months,

–
*Muscle mass criteria*: lean body mass (LBM) estimated by bioimpedance spectroscopy (Body Composition Monitor (BCM) Fresenius, Bad Homburg, Germany) lower than the 10^th^ percentile of an aged-matched normal population. This method is validated in dialysis patients [33,34].

–Dietary intake criteria: Unintentional low dietary protein intake < 1 g/kg of ideal weight/day for at least 2 months, unintentional low dietary energy intake < 30 kcal/kg of ideal weight/day for at least 2 months.

•Informed consent of the patient.

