### Primary outcome measures

The primary outcome of this study is the number of patients who are no longer in a state of protein energy wasting after 6 months of exercise training compared to the control group. We define correction of PEW as the normalization of albumin and prealbumine, and of the lean tissue index, considering these items to be the clinically most relevant for the diagnostic criteria of PEW.

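### Patients enter with one, two or three components of the primary outcome abnormal, and the stated analysis takes no account of this strong predictor of correction

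*Protocol article*

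**What the plan says.** **Entry (Protocol article, Inclusion criteria).** Patients qualify by "meeting at least three out of the four listed categories and at least one test in each of selected category". The categories are:
- serum chemistry: "Serum albumin level < 38 g/L (Bromcresol Green), or serum prealbumin < 300 mg/L", so one low protein is enough;
- body mass: "BMI < 23 kg/m^2^, or unintentional weigh loss > 5% over 3 months or > 10% over 6 months";
- muscle mass: "lean body mass (LBM) estimated by bioimpedance spectroscopy", "lower than the 10^th^ percentile of an aged-matched normal population";
- dietary intake: "Unintentional low dietary protein intake < 1 g/kg of ideal weight/day for at least 2 months", or low energy intake.

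**Outcome (Primary outcome measures).** "We define correction of PEW as the normalization of albumin and prealbumine, and of the lean tissue index". Body mass and diet play no part in it.

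**Allocation (Study design).** "The randomization sequence of the participants will be generated by a computer program". No stratification factor is named.

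**Analysis (Statistical analysis).** For all outcome measures, a two-way ANOVA is stated with Group between subjects and Time (t0, t+2, t+4, t+6) within subjects. No term for baseline component status or entry route appears.

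**The concern.** The entry rule and the outcome overlap only in part. One patient may need a single blood value to cross its cut-off to count as corrected. Another must regain lean tissue and raise one or both proteins by week 24. How many outcome components are abnormal at t0, and above all whether lean tissue is among them, should therefore predict correction strongly whatever the treatment.

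Having t0 as a level of Time does not deal with this for the primary outcome. If entry and outcome use the same lean-tissue measure, every patient is uncorrected at t0, so the t0 value of the binary outcome says nothing about how far each patient has to go.

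At stake in a trial of about fifty patients are precision, protection against chance imbalance, and what the overall proportion corrected means.

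**Working it through.** **1. Abnormal outcome components at entry.** I take normalisation to mean being in the normal range at 6 months, and assume that entry and outcome use the same lean-tissue measure. Going through every on/off pattern of albumin, prealbumin, body mass, lean tissue and diet that satisfies the entry rule gives:

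| Categories met | Outcome components abnormal at t0 |
|---|---|
| body mass + muscle + diet | 1 (lean tissue only) |
| serum + body mass + diet | 1 or 2 (lean tissue not low) |
| serum + muscle + diet | 2 or 3 |
| serum + body mass + muscle | 2 or 3 |
| all four | 2 or 3 |

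Zero is impossible, because only two of the four categories lie outside the outcome and entry needs three.

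**2. How much difficulty can differ.** As an illustration, assume independent components, each normalising with probability 0.30 (control) or 0.60 (exercise), and normal components staying normal. With k abnormal components, P(correction) = q^k:
- k = 1: 0.30 against 0.60
- k = 2: 0.30² = 0.09 against 0.60² = 0.36
- k = 3: 0.30³ = 0.027 against 0.60³ = 0.216

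**3. Precision.** The article states 22 per group at alpha 0.05 and 80% power but gives no correction rates, so that figure can be neither reproduced nor refuted. A two-sided test without continuity correction fits, for example, about 10% against 48% or 30% against 72%. I use 22 per arm as given.
- Simulation with per-component probabilities of 0.30 and 0.70 and an equal mix of k = 1, 2 and 3: power is 77% for the crude comparison and 80% for a Cochran-Mantel-Haenszel test stratified by k.
- Other mixes gain less: 76.9% to 78.7% for shares of 60/30/10% with k = 1, 2, 3, and 81.7% to 82.2% for 10/30/60%.
- Two strata by baseline LTI, with assumed correction rates of 10% (low) and 50% (not low): about 59% crude and 65% stratified. The size also depends on the exercise effect assumed.
- With no treatment effect (per-component probability 0.50 in both arms), the crude test rejects in 4.7% and 5.2% of runs for the 60/30/10% and equal mixes.

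**4. Chance imbalance.** Assume simple randomisation, 25 per arm, and low-LTI counts that are independent Binomial(25, p). P(difference of 5 or more patients) is:

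| p (low LTI at t0) | 0.5 | 0.6 | 0.7 | 0.8 | 0.9 |
|---|---|---|---|---|---|
| Probability | 0.20 | 0.19 | 0.16 | 0.11 | 0.03 |

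The documents do not give p. The Background cites 62% with diminished lean body mass in a French cohort, but those were haemodialysis patients in general, judged by a different cut-off. Selection for PEW should raise the share. Suppose 62% before selection and the other three categories independent, each met with probability c:
- c = 0.7: P(at least 2 of 3) = 0.784 and P(3 of 3) = 0.343. The share with low lean mass is 0.62 × 0.784 / (0.62 × 0.784 + 0.38 × 0.343) = 0.79.
- c = 0.3: the two probabilities are 0.216 and 0.027. The share is 0.62 × 0.216 / (0.62 × 0.216 + 0.38 × 0.027) = 0.93.

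The lower probabilities in the table are therefore the likelier ones.

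**5. Size of a shift.** With the assumed 10% and 50% rates, a 20-point imbalance (5 of 25) moves the arm difference by 0.20 × (0.50 − 0.10) = 0.08 with no treatment effect. At p = 0.6 the pooled rate is 0.6 × 0.10 + 0.4 × 0.50 = 0.26, and the standard error of the arm difference is √(2 × 0.26 × 0.74 / 25) = 0.124. The shift is smaller than one standard error.

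**The case against.** The strongest reply is that this is ordinary baseline heterogeneity. Randomisation balances it in expectation, the test keeps its level, and an 8-point shift lies within sampling error that a valid test already allows for. The three-of-four rule is the published diagnostic rule, and the article gives its reason for choosing these outcome components. All of that stands. It makes this a matter of efficiency and interpretation, not of validity.

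Four stronger readings are tempting, and the documents do not support them.
- *Entry route biases the comparison.* It does not; only chance imbalance is possible.
- *A patient could already meet correction at t0*, because entry names lean body mass and the outcome names LTI in kg/m². This depends on reading the Inclusion criteria alone. Participants' recruitment says that lean body mass index is measured by bioimpedance, so an index was probably meant at entry too. What remains is inconsistent wording.
- *The trial cannot tell regained lean tissue from a change in a blood marker.* Secondary outcome measures list albumin, prealbumin and LTI as separate outcomes, so effects on each will be visible. Only the pooled primary proportion is hard to interpret.
- *Randomisation is unstratified.* The article is condensed and does not say so. The absence of a named factor is silence, and the probabilities in step 4 are conditional on simple randomisation.

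The analysis is on a different footing. The article does state a model for all outcome measures, and that model contains only Group and Time. A fuller document may add adjustment, but the model as printed does not.

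**Conclusion.** The point holds as one of precision and interpretation. That patients enter with one, two or three outcome components abnormal follows from the printed entry and outcome rules and needs no assumed figure beyond a common lean-tissue measure. That the printed analysis does not use this is plain from its two factors.

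The size is modest: about 3 to 6 power points in the more favourable illustrations, and less when most patients share the same number of abnormal components. The probability of an imbalance of 5 or more low-LTI patients is about 20% down to 3% as prevalence goes from 50% to 90%. The correction rates, the independence of components, the prevalence and simple randomisation are all assumptions. Type I error is not affected. A result from one mix of entry routes will not carry over directly to another, so the overall proportion corrected should not stand alone.

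**What to change.** - **Analysis.** Compare correction at 6 months between arms with stratification of the analysis by, or adjustment for, baseline LTI status. A Cochran-Mantel-Haenszel test with two strata (low or not low at t0) is enough.
- **Reporting.** Give the proportion corrected by arm separately for patients with and without low LTI at t0, beside the overall figure.
- **Wording.** Reconcile lean body mass (Inclusion criteria), lean body mass index (Participants' recruitment) and lean tissue index (Primary outcome measures), so that entry and outcome clearly use the same BCM measure.

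The cost is one two-level factor, one extra table and a wording change. LTI at t0 is already planned under Outcome measures and Body composition, so no further measurement or patient is needed. If nearly all patients turn out to have low LTI, the stratified test gains little and loses little.

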### Exclusion criteria

•Contraindication or inability to perform the physical exercise.

•Inadequate dialysis Kt/V < 1.2.

•Presence of a cardiac pacemaker (incompatible with the BCM measures).

•Systemic inflammation CRP > 20 mg/l.

•Pregnant woman.

•Patient under guardianship.

•Participation in another clinical interventional trial.

•Unstable on dialysis.

### Intervention

All the patients will continue their usual dialysis procedure (HD or HDF). No modifications of dialysis modality or prescriptions are allowed except for adaptation of dry weight using clinical criteria.

Both patients in the control and exercise groups will receive dietary counseling by a trained dietician. The prescription of oral nutritional complements or intradialytic parenteral nutrition will be adapted to patient needs according to the dietary record in order to attain goals set by the EBP guidelines for gender energy intake 30–40 kcal/kg of ideal weight/day, and protein intake > 1.1 g/kg of ideal weight/day.

### Exercise group

A 6-month adapted rehabilitation program will be conducted by means of progressive submaximal individualized cycling exercise, consisting of three sessions per week. The exercise will be prescribed during the first two hours of dialysis session using an adapted cycle ergometer (« Reck moto-med letto ») that allows cycling in a supine position at different resistance levels. The cycle ergometer displays the number of revolutions per minute, the power developed and the distance virtually traveled. For the patient, these types of visual feedback are motivational factors that are recognized in the literature [35]. Further, it should be noted that this cycle ergometer also allows for passive motorized pedaling (i.e., the patient can pedal without effort).

The aim of this 6-month individualized program is to reach a 30 min duration of continuous cycling at a moderate exercise intensity, which corresponds to the level “3 – moderate” on the Borg Rating Perceived Exertion (RPE) scale (graduated from 0 to 10, where 0 = no effort at all, and 10 = most extreme effort imaginable). According to recommendations issued from a large scale meta-analysis [36], the exercise will be initially performed at this intensity exercise perceived as moderate by the patient on the RPE scale (i.e., level 3). We deliberately chose this method based on the patient’s rating perceptions rather than a method based on the heart rate assessment because many dialysis patients have automatic impairment or drug treatments that can interfere with the heart rate control. This method is readily accessible, reproducible and easy to use. Several exercise training intensity levels at 50% to 85% of the maximal oxygen consumption correspond consistently to ratings of 3–7 levels on the Borg RPE scale [37].

To estimate the targeted moderate exercise intensity, an exercise protocol with an increasing intensity on the cycle ergometer will be performed at the inclusion, before the rehabilitation program. During this first evaluation, after a warm-up of 5 minutes without resistance, the patient will pedal with a self-selected chosen cadence against an increasing resistance imposed by the cycle ergometer, until the patient reaches a level perceived as moderate, namely level 3 on the Borg RPE scale. A similar monthly assessment will be realized to update the intensity of cycling exercise. During these sessions, the patient will be regularly asked about level of shortness of breath, any feelings of fatigue and pain, with a visual analogue scale (0–10 cm), in order to reduce the exercise intensity if necessary.

During a dialysis session, the cycling exercise will be performed in the first half of the session. After a 5 min warm-up without resistance, the patient will gradually reach the intensity corresponding to level 3 on the Borg RPE scale. Then the patient will be instructed to maintain this cycling exercise intensity for at least 10 minutes during the first month, 15 minutes during the second one, 20 minutes for the two next months in order to achieve the targeted exercise duration of 30 minutes in the two last months. The first target is to observe an evolution of their functional capacity/performance over time. Finally, a period of active recovery (pedaling without resistance) followed by a period of passive pedaling recovery will end the exercise session. Blood pressure and heart rate will be measured at the beginning and the end of the exercise session. Heart rate will be maintained below 70% of maximum heart rate during the cycling exercise. At the end of the dialysis session, the HD patient will be asked to estimate pain level, boredom level and mood as perceived during the session, with a visual analogue scale graduated from 0 to 10. Nephrologists, nurses, and a specialist in adapted physical activities will monitor the patient.

